#### Participation rate and treatment acceptability

Evaluation of participation rate and treatment acceptability will be based on the descriptive statistics, that is, percentage of participants who sign up to the study and complete it, the percentage from each group who drop out at each stage and mean scores on treatment acceptability questionnaire. Ninety-five per cent CIs for participation rate and acceptability scores will be calculated, which will show the upper and lower bound values of where the true population parameter will appear. Formal tests will be conducted to compare participant rates between the two groups (χ^2^ analysis). For treatment acceptability, χ^2^ tests will test the proportion of participants selecting each response option.

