**Trial registration number:**

NCT03062891; Results.

Strengths and limitations of this studyThis study contains a large sample size for a pilot study and will provide valuable effect size information useful for the planning of future investigations of this topic.Stratification on sleep problems was implemented to ensure baseline sleep problems were equal in both groups.Recruitment was done using convenience sampling, which may lead to some self-selection bias in the sample.The online nature of the study makes it difficult to fully assess adherence to the intervention.

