### Participation rate and treatment acceptability

The second aim of the study is to assess the feasibility of a digital CBT-I intervention study in a non-clinical group. For example, will participants without insomnia be willing to complete a 6-week online programme aimed at improving sleep? As such, we will be closely monitoring participation (the proportion of participants who are willing to take part in the study) and drop-out rates (the percentage of participants who sign up to the study and drop out before the end of the study). We will also examine treatment acceptability. While psychological interventions to treat insomnia such as CBT-I have been rated highly by patients with regards to how acceptable they find the treatment,^27 28^ it is important for this study to investigate whether participants who do not necessarily have a sleep disorder find CBT-I an acceptable treatment. This will be assessed using an adapted version of the Treatment Acceptability Questionnaire (TAQ)^29^; for more information, see the Measures section.

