### Participant recruitment

Participants were recruited to the study using a two-step procedure. Initially, potential participants were contacted via an e-mail that provided the study information, specific instructions as to the nature of the recruitment day and contact information.

The second stage of recruitment involved a series of recruitment days at the three sites. These recruitment days were timed to coincide with classes that potential participants were present at, to make it more likely that they would be in university. At sign-up, participants were given a paper copy of the information sheet and were given the option to ask any questions about the nature of the study. After confirming that they were happy to take part in the study, all participants were asked to give informed consent, provide a DNA sample (see the DNA sample collection section) and were assigned a unique participant ID number, which was used for future assessments. To allow the participation of individuals who wished to take part in the study but were unable to sign up in person, participants were given the option to contact the research team directly by email in order to arrange providing consent to take part in the study.

Participants were rewarded for their time, either in the form of course credits (offered credits + £5 online gift voucher) or online shopping voucher (£40), awarded to them on completion of the study.

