## Intervention

### Digital CBT-I

CBT-I participants received six weekly CBT-I sessions delivered by an animated ‘virtual therapist’ (The Prof) via the online platform ‘Sleepio’ (http://www.sleepio.com). The programme comprised a fully automated media-rich web application, driven dynamically by baseline, adherence, performance and progress data, and provides additional access to elements such as an online library with background information, a community of fellow users and support, prompts and reminders sent by email.

The Sleepio programme covers behavioural (eg, sleep restriction, stimulus control) and cognitive (eg, putting the day to rest, thought restructuring, imagery, articulatory suppression, paradoxical intention, mindfulness) strategies, as well as additional relaxation strategies (progressive muscle relaxation and autogenic training) and advice on lifestyle and bedroom factors (sleep hygiene). As part of the intervention, participants filled in a daily sleep diary. The intervention was based on a previously validated manual.^37–39^ Sleepio has been shown to improve sleep and associated daytime functioning in adults diagnosed with insomnia disorder.^11^

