### Puzzles

Participants in the control group were sent weekly puzzles to complete within Qualtrics. Each puzzle was designed to be cognitively engaging, and time taken to complete a puzzle was matched as closely as possible to the time taken to complete one session of digital CBT-I. Puzzles were sent directly to participants via automated distribution emails sent at 7-day intervals. In order to track whether participants were completing the puzzles, they were required to enter their participant ID number at the start of each puzzle. The types of puzzles administered to participants included word searches, crosswords and lateral thinking problems.

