### Waves 2–4 data collection

The second and third waves of data collection were carried out 3 weeks and 6 weeks following allocation. The fourth wave was carried out 6 months following the allocation of participants to groups. These time points corresponded to mid-intervention, end-of-intervention and post-intervention follow-up time points, respectively (see figure 1 for more detail). Automated emails distributed by Qualtrics were sent to participants at the designated intervals. Not all measures are assessed at all waves, as shown in table 1. Follow-up emails to non-responders were sent each week to participants who fall behind on their tasks (ie, CBT-I, puzzles or surveys).

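### The pilot asks whether people without insomnia will complete a 6-week programme, but its stated completion and drop-out measures are defined on the whole study, so they do not answer that question

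*Protocol article*

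**What the plan says.** The protocol article's second primary aim (Primary objectives, Participation rate and treatment acceptability) is the feasibility of a digital CBT-I study in a non-clinical group. Its example question is "will participants without insomnia be willing to complete a 6-week online programme aimed at improving sleep". The same paragraph defines drop-out as "the percentage of participants who sign up to the study and drop out before the end of the study". The section of the same name under Statistical analysis says that evaluation rests on the "percentage of participants who sign up to the study and complete it, the percentage from each group who drop out at each stage", together with mean acceptability scores. Neither section names sessions completed as an outcome, and neither says what completing the study, or a stage, consists of.

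Other sections bear on this:

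- Design and Table 1: surveys at baseline, 3 weeks, 6 weeks and 6 months; the intervention occupies the first 6 weeks.
- Participant recruitment: the reward (credits plus £5, or £40) is "awarded to them on completion of the study".
- Waves 2–4 data collection: weekly follow-up emails go to "participants who fall behind on their tasks (ie, CBT-I, puzzles or surveys").
- Digital CBT-I: the platform is "driven dynamically by baseline, adherence, performance and progress data".
- Puzzles: "In order to track whether participants were completing the puzzles, they were required to enter their participant ID number".
- Strengths and limitations: "The online nature of the study makes it difficult to fully assess adherence to the intervention".
- Judging study success: participation rates, acceptability and effect size are weighed together, without strict criteria.

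**The concern.** The question concerns exposure to a 6-week programme. The stated measures concern presence in a 6-month study made up of surveys as well as an intervention. These are different events with different end dates, and neither implies the other.

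Participation rate is one of three inputs to the decision on the larger study. That study is meant to look for predictors of response to CBT-I, and the Sample size section says that variance, not the mean difference, is the statistic of main interest. If some participants receive little of the programme, the spread of SCI change in the CBT-I arm mixes differences in response with differences in exposure, and a study-level retention figure will not show it. Conversely, losses at the 6-month survey could make the programme look less feasible than it was.

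**Working it through.** **1. Question against measure.** No stated figure is in dispute here, so the first check is to set the wording side by side.

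| Item | Refers to | Ends at |
|---|---|---|
| Example question under the second primary aim | the online programme | 6 weeks |
| Drop-out definition, same paragraph | the study | 6 months |
| Planned completion percentage | the study | 6 months |
| Planned drop-out by group and stage | the study; stages undefined | not stated |

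**2. Can the two diverge, as worded?** Two cases:

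- All surveys answered, few or no sessions done. This person has not left before the end of the study, so the drop-out definition does not capture them.
- All six sessions done, 6-month survey missed. The programme was completed, but the person may be counted as having dropped out before the end.

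The measure can therefore err in either direction. The article itself treats the components as separable: it lists CBT-I, puzzles and surveys as distinct tasks and plans weekly reminders for people who lapse on any of them.

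**3. Illustration of size.** The only related figures are in Sample size: a target of 200 and recruitment of 240. No attrition rate is stated. The implied rate is 1 − 200/240 = 16.7% by N/(1 − d), or 240/200 − 1 = 20% by N × (1 + d).

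Assumptions: 1:1 allocation (not stated), giving 240/2 = 120 in the CBT-I arm, and 100 of these completing the study, in line with 16.7% attrition. Let s be the share of study completers who did not do the sessions, and t the share of the 20 non-completers who nevertheless did all six. Then

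programme completers = 100 × (1 − s) + 20 × t.

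With Wilson 95% intervals on n = 120:

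| s | t | Count | Rate | 95% CI |
|---|---|---|---|---|
| study completion | – | 100 | 83.3% | 75.7–88.9 |
| 0.1 | 0 | 90 | 75.0% | 66.6–81.9 |
| 0.3 | 0 | 70 | 58.3% | 49.4–66.8 |
| 0.5 | 0 | 50 | 41.7% | 33.2–50.6 |
| 0 | 0.5 | 110 | 91.7% | 85.3–95.4 |

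The values of s and t are assumptions; the documents give none. The table shows only that a study completion rate does not determine the programme completion rate.

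**4. Are the data for the right measure available?** Puzzle completion is tracked by participant ID. Reminders to people behind on CBT-I require knowledge of who is behind, and the platform runs on adherence and progress data. A count of sessions is a much smaller demand than the full assessment of adherence that the article calls difficult.

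**The case against.** The strongest reply is that completion and stage are undefined, and that the article lists CBT-I among participants' tasks. Completing the study could then include doing the sessions, stages could include the intervention period, and the reward could depend on sessions as well as surveys. A full protocol or analysis plan that is not shown may say so. The stated aim is also the feasibility of a study, with the programme question introduced only as an example, and acceptability is measured separately.

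Much of this stands, and it limits the point. A reader might infer that the pilot measures nothing except completion of the paid study, or that someone who skips the sessions but fills in the surveys is scored as a success. The article supports neither. Task completion is followed in both arms, no rule classes any participant as a success, and the success judgement has no strict criteria. Nor does the text show that payment is for surveys alone.

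The mismatch remains. The drop-out definition is printed in the article, not left to another document, and it refers to the study directly after a question about the programme. Including sessions in study completion would not resolve it either: a single composite that also requires the 6-month survey still does not say how many people finished the programme. The acceptability questionnaire records opinions, not sessions done. The disclosed limitation concerns full assessment of adherence and does not rule out a session count.

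**Conclusion.** The point holds as a mismatch between a stated question and its stated measure. Study completion and drop-out do not answer whether participants will complete the 6-week programme, and they can misstate it in either direction. No figure in the article is wrong.

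The size is unknown because no session rates are given. Under the assumptions above (120 per arm, 100 study completers), a reported 83.3% is compatible with programme completion of 41.7% to 91.7% across the scenarios shown. This range illustrates the possible gap and does not predict it.

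The change is worth making, because the measure belongs to a primary objective and feeds the decision on the larger study.

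**What to change.** In Statistical analysis, Participation rate and treatment acceptability:

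- Add programme completion as a separate feasibility outcome: Sleepio sessions completed (0-6) from platform records, and puzzles completed (0-6) from the ID logs.
- Report the distribution by arm, and the percentage completing all six by wave 3 with a 95% CI, with everyone randomised to that arm as the denominator.
- Report survey retention at each wave separately, and state what completion and stage mean for it.

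In Judging study success, consider both: programme completion for the question asked under the second primary aim, and survey retention for the feasibility of measuring SCI change. Survey retention should not be dropped, because change scores cannot be computed without the follow-up surveys.

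The cost is a few sentences and a small export of session and puzzle logs. The drawback is that the feasibility figure may be less favourable than study completion alone.

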### Secondary objectives

#### Factors predicting treatment outcome and sleep quality and implications for associated variables

We will test which measures at baseline are moderators of longitudinal outcome of change scores in insomnia symptoms with multivariate generalised estimating equation models using Akaike/Bayesian information criteria to select an optimal model with predictors of insomnia symptoms/sleep quality derived. All models will be run in Stata and control for covariates (eg, age) and the non-independence of sibling-pair data. Missing data shall be accounted for using maximum likelihood or multiple imputation procedures. Due to the small sample size, power may not be sufficient to investigate interaction effects. However, they shall be performed as an exploratory analysis.

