**Methods and analysis:**

A two parallel-group randomised controlled trial is being conducted across three London universities. Female students (minimum age 18 years) enrolled on a psychology programme at one of the three sites were invited to participate. The target number of participants to be recruited is 240. Following baseline assessments, participants were randomly allocated to either the treatment group, where they received weekly sessions of digital CBT-I for 6 weeks, or the control group, where they completed an online puzzle each week for 6 weeks. Follow-up assessments have taken place mid-intervention (3 weeks) and end of intervention (6 weeks). A 6-month follow-up assessment will also occur. Primary outcomes will be assessed using descriptive statistics and effect size estimates for intervention effects. Secondary outcomes will be analysed using multivariate generalised estimating equation models.

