### Design

The study was a two-group parallel randomised controlled trial in which the intervention group received a digital CBT-I intervention and the control group received a weekly online puzzle. See the Intervention section for more details.

Participants were female students (both undergraduate and postgraduate) completing a psychology programme at one of three London universities (for full details, see the trial registration). After completing the baseline assessment online via the Qualtrics system, participants were randomly allocated to either the CBT-I or puzzles group. Three weeks later, participants completed a second online assessment and then a third online assessment 6 weeks after the start of the study. Finally, a follow-up online assessment was carried out 6 months after group allocation. Participants were also invited to give a DNA sample at the start of data collection. While we have limited statistical power to look at genetic predictors of treatment outcomes in the pilot study, these samples could be pooled with other data collected in the future and also provide a useful opportunity for our collaborators to collect data for another ongoing research initiative.^34^ See figure 1 for a detailed outline of the study timeline. A completed Standard Protocol Items: Recommendations for Interventional Trials checklist and WHO trial registration data set can be found in online supplementary files 1 and 2.

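### The secondary GEE models are to be selected by AIC/BIC, which GEE does not define, and the only clustering named is sibling pairs, which this trial does not recruit

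*Protocol article*

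**What the plan says.** The protocol article's statistical analysis section on secondary objectives makes three commitments.

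- **Model and selection rule.** Baseline measures are to be tested as "moderators of longitudinal outcome of change scores in insomnia symptoms", in multivariate GEE models, "using Akaike/Bayesian information criteria to select an optimal model with predictors of insomnia symptoms/sleep quality derived". The abstract repeats the model choice: "Secondary outcomes will be analysed using multivariate generalised estimating equation models".
- **Missing data.** "Missing data shall be accounted for using maximum likelihood or multiple imputation procedures".
- **Dependence.** All models are to "control for covariates (eg, age) and the non-independence of sibling-pair data".

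The design section describes the sample: "Participants were female students (both undergraduate and postgraduate) completing a psychology programme at one of three London universities". On timing, the data collection section says "The second and third waves of data collection were carried out 3 weeks and 6 weeks following allocation", with a fourth wave at 6 months. Each participant can therefore contribute a baseline and up to three follow-up assessments of the Sleep Condition Indicator (SCI).

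**The concern.** The parts of this specification do not fit together. The selection rule needs a likelihood and the model has none. One of the two missing-data routes needs a likelihood as well. The one source of dependence that is named belongs to a design with related participants, whereas this trial enrols individual students.

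What is at stake is which predictors are kept and what effect sizes are reported for them. The secondary aims section says that these effect sizes will inform power calculations for a larger behavioural genetics study, and Table 1 supplies many candidate predictors. An analyst who follows the text literally must replace the criterion with something the protocol does not name. If that replacement is whatever number a software package prints, the selection may be too liberal.

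**Working it through.** The protocol states no figure to reproduce here. The check sets its statements against each other, and one calculation on assumed inputs shows why the criterion matters.

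**1. Model against selection rule.** AIC = −2 log L + 2k, and BIC replaces 2k by k log n, where L is the maximised likelihood and k the number of parameters. GEE solves estimating equations built from a mean model and a working correlation. No joint likelihood is maximised, so there is no L to insert. The usual analogue is QIC, or QICu for choosing the terms in the mean model.

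Software output does not settle this. In a check on simulated data, one package did print values after a GEE fit: AIC 1686 and BIC −3241. The AIC came from an independence likelihood and the BIC was on a different scale. Neither is a valid criterion for correlated data.

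**2. What an independence-likelihood AIC would do.** The protocol gives no within-person correlation, so the inputs are assumptions: three follow-up waves and an equal correlation ρ between them.

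- One extra parameter is retained when twice the log-likelihood gain exceeds 2. With a correct likelihood and a null term, the chance is 2 × [1 − Φ(√2)] = 15.7%.
- For a predictor fixed at baseline, ignoring the correlation inflates the gain by about 1 + 2ρ. The chance becomes 2 × [1 − Φ(√(2/(1 + 2ρ)))].

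| ρ (assumed) | 1 + 2ρ | Null term retained |
|---|---|---|
| 0.4 | 1.8 | 29.2% |
| 0.5 | 2.0 | 31.7% |
| 0.6 | 2.2 | 34.0% |
| 0.7 | 2.4 | 36.1% |

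The value 0.5 has a structural basis for change scores. If all four assessments have equal variance σ² and equal correlation r, two changes from the same baseline have covariance σ²(1 − r) and variance 2σ²(1 − r). Their correlation is then 0.5 whatever r is.

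A simulation agrees. It used 200 participants, three waves, ρ = 0.6, no true moderators and 300 tests of a moderator-by-group term. The independence-likelihood AIC retained the null term in 37.7% of tests (Monte Carlo standard error √(0.377 × 0.623/300) = 2.8 points). A random-intercept model fitted by maximum likelihood retained it in 17.3% (standard error 2.2 points).

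**3. Missing-data options.** Maximum likelihood under missing at random (MAR) requires a likelihood for the repeated outcomes, which GEE lacks. Multiple imputation followed by GEE is valid under MAR. One option therefore fails and one stands.

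**4. Named clustering against the design.** The sections on design, eligibility, recruitment and randomisation describe students who sign up individually and are allocated individually, stratified by age, sleep problems and site. No step recruits, identifies or links siblings, and Table 1 lists no sibling item. Twins appear only in the plans for the future study, in the introduction and primary objectives. The dependence that does exist is between waves of the same participant. The word longitudinal implies it, but the text does not name participant as the cluster.

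**The case against.** The strongest case on the other side is that this is a wording problem in secondary text. Much of it stands.

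- GEE with multiple imputation can be run as described; only the criterion needs replacing. A reader might infer that the whole secondary analysis cannot be carried out, or that the model must be changed after the data are seen. The document supports neither. A statistical analysis plan could fix the criterion beforehand.
- A reader might infer that naming sibling pairs means the repeated waves will be analysed as independent rows, so that tests of baseline predictors exceed their nominal error rate. That does not follow. GEE for a longitudinal outcome is chosen to handle such correlation. With no pairs enrolled, a family cluster is simply one participant with all her waves. If two sisters did enrol by chance, their waves would sit inside the larger cluster.
- A reader might infer that the results will rest on data missing completely at random, as GEE on available cases generally requires. The protocol offers multiple imputation, so that reading supposes that its own sentence is ignored.
- A reader might take 40/240 as the planned attrition. The sample size section states no rate; it gives only a target of 200 and recruitment of 240 to allow for some loss.
- The primary analyses of SCI change, participation and acceptability do not use GEE. The article warns that power for effects on associated variables may be lacking, and it labels interaction effects exploratory.

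These points limit the consequences. They do not make AIC or BIC defined for GEE, make maximum likelihood available within it, or give the sibling clause anything to refer to.

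**Conclusion.** The point holds as an error in what is written, not as an omission that a later document would fill. The selection rule is undefined for the named model, one of the two missing-data options is unavailable within it, and the only clustering named is absent from this trial while the real one is left implicit.

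Severity is moderate. The effect is limited to the secondary analyses of a pilot, but the predictors and effect sizes they yield are meant for planning the larger study. The 29% to 36% retention range illustrates one possible substitute, an AIC from an independence likelihood. It rests on three waves, equal correlation of 0.4 to 0.7 and a predictor fixed at baseline. It does not predict what the analysts will do.

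**What to change.** Choose one of two routes and state it in the secondary objectives text.

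1. **Keep GEE.** Name participant ID as the cluster, replace AIC/BIC with QIC/QICu, and give multiple imputation as the only missing-data method. This is the smaller edit.
2. **Keep AIC/BIC.** Replace GEE with a linear mixed model with participant random effects, fitted by maximum likelihood rather than REML so that models with different fixed effects can be compared. Missing outcomes are then handled under MAR. Participants may skip any question, so impute missing baseline predictors as well, so that all candidate models are compared on the same records. The abstract's sentence on GEE would need to change too.

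Under either route, remove the sibling-pair clause, or explain which participants it refers to and how they are identified.

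The cost is a few sentences of analysis text and, for the second route, a different model command. No new data are needed and the primary analyses are unaffected.

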Investigations of predictors of treatment response to CBT applied to other conditions, such as anxiety, have shown a wide range of demographic, clinical, genetic and epigenetic factors influence response to CBT treatment for anxiety.^16–19^ Genetic predictors of treatment outcome are still unclear however. While some studies have reported specific genetic markers for intervention outcome in disorders such as post-traumatic stress disorder,^20^ panic disorder^21^ and social anxiety disorder,^22^ these findings have not always been replicated.^23 24^ While individually, any genetic predictor is likely to only explain a small proportion of variance in treatment outcome, understanding these multiple factors and their interactions may serve an important role in improving the outcome of therapy. The aim of this pilot study is to test the feasibility of running a larger-scale study of predictors of treatment outcome for CBT-I within a twin design, where not all participants will have insomnia.

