## Secondary aims

### Factors predicting treatment outcome

We will collect data on factors that may predict treatment outcome and will be able to use the data collected to estimate effect sizes for various predictors, which will be useful in power calculations to estimate the sample size for a larger future behavioural genetics study. Furthermore, by including these measures in the pilot study, it will allow us to assess the feasibility of administering a large battery of questionnaires to participants in addition to completing the digital CBT-I/puzzles.

Based on previous work into predictors of treatment outcome in CBT for anxiety,^16–19^ a wide range of demographic, clinical and genetic predictors such as potential single-nucleotide polymorphisms and polygenic risk scores of response to digital CBT-I will be investigated (see the Measures section for more details) for producing an estimated effect size that will be helpful in the planning of a larger study.

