### Sample size

For this study, the target was to have 200 participants, which should provide power to examining our primary research questions, though we plan to over-recruit to account for some attrition throughout the study. As such, 240 participants will be recruited. Power analyses are often conducted using hypothesised effect sizes based on mean differences (eg, before and after treatment). However, as this is a pilot for a future behavioural genetics study, the main statistic of interest is not mean differences but individual differences (ie, variances). The decision to recruit 200 participants for this pilot study was mainly based on personal experiences of recruiting undergraduates from our institutions.

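### Predictor effect sizes are wanted for powering the larger study, but the only predictor analysis described is AIC/BIC selection of one model in about 200 people; estimates taken from that model would overstate weak predictors.

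*Protocol article*

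**What the plan says.** Under Secondary aims, Factors predicting treatment outcome, the protocol article says that the authors "will be able to use the data collected to estimate effect sizes for various predictors, which will be useful in power calculations" for a larger behavioural genetics study. The same section repeats the purpose, "for producing an estimated effect size that will be helpful in the planning of a larger study", and describes the candidates as "a wide range of demographic, clinical and genetic predictors", including single-nucleotide polymorphisms and polygenic risk scores.

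The method is in Statistical analysis, Secondary objectives. Baseline measures are tested as moderators of change in insomnia symptoms with multivariate GEE models, "using Akaike/Bayesian information criteria to select an optimal model with predictors of insomnia symptoms/sleep quality derived". Covariate adjustment and missing-data handling are mentioned. The section admits that power for interactions may be insufficient and calls them exploratory. It describes no second predictor model, shrinkage, resampling or hold-out sample.

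Under Sample size, "the target was to have 200 participants", and to allow for attrition "240 participants will be recruited". The Introduction says that "any genetic predictor is likely to only explain a small proportion of variance in treatment outcome".

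**The concern.** The aim is estimation: a usable effect size for each of several predictors. The method is selection: search many candidates and keep those that improve an information criterion. A coefficient in the selected model is seen only because it passed a threshold. For a strong predictor this hardly matters, because it nearly always passes. A weak predictor passes mainly in samples where chance has pushed its estimate up, so the average retained estimate lies above the truth.

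At stake is the use the protocol names for these figures. A sample size varies roughly with the inverse square of the effect, so an effect overstated by half calls for less than half the people needed. Predictors dropped from the model would leave no figure with which to plan.

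**Working it through.** **The plan's own figure.** The target of 200 has no alpha, power or effect size behind it; the protocol rests it mainly on recruitment experience. It therefore cannot be reproduced from a power formula. The step to 240 implies an allowance of 1 − 200/240 = 16.7% for attrition.

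**Inputs.** From the protocol: n = 200, many candidates, AIC or BIC selection. Assumed, because no figures are given: true standardised effects r from 0.05 to 0.30; standard error 1/√n; a Gaussian likelihood in place of GEE; and, for the larger study, two-sided alpha 0.05 and 80% power.

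**Step 1, threshold.** Adding one predictor lowers AIC if |z| exceeds about √2 = 1.41, and lowers BIC if |z| exceeds about √(ln 200) = 2.30. Divided by √200 = 14.14, the smallest effect that can be kept is about 0.10 (AIC) or 0.163 (BIC). For a difference in slopes between two equal arms the standard error doubles, and the floors become about 0.20 and 0.33.

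**Step 2, mean kept estimate.** With δ = r√n, threshold c, P₁ = Φ(δ − c) and P₂ = Φ(−δ − c):

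mean kept |estimate| = [δP₁ + φ(c − δ) + φ(c + δ) − δP₂] / [√n (P₁ + P₂)]

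For r = 0.10, δ = 1.414.
- AIC: (0.7071 + 0.3989 + 0.0073 − 0.0033) / (14.142 × 0.5023) = 1.110/7.104 = 0.156.
- BIC: (0.2650 + 0.2691 + 0.0004 − 0.0001) / (14.142 × 0.1875) = 0.5344/2.652 = 0.202.

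**Step 3, size and true power of the larger study.** N = ((1.96 + 0.842)/atanh r)² + 3, rounded up.
- Needed for a true 0.10: 783.
- Planned on the AIC estimate: 320, with true power Φ(0.1003 × √317 − 1.96) = 43%.
- Planned on the BIC estimate: 192, with true power Φ(0.1003 × √189 − 1.96) = 28%.

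**Range at n = 200 (AIC / BIC):**

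| True r | Kept | Mean kept estimate | Planned N | Needed N | True power |
|---|---|---|---|---|---|
| 0.05 | 26% / 6% | 0.141 / 0.193 | 395 / 210 | 3138 | 17% / 11% |
| 0.10 | 50% / 19% | 0.156 / 0.202 | 320 / 192 | 783 | 43% / 28% |
| 0.15 | 76% / 43% | 0.179 / 0.215 | 244 / 168 | 347 | 65% / 49% |
| 0.20 | 92% / 70% | 0.211 / 0.235 | 174 / 140 | 194 | 76% / 66% |
| 0.30 | 99.8% / 97% | 0.301 / 0.304 | 85 / 83 | 85 | 80% / 79% |

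With all 240 analysed, the overstatement at 0.10 is 1.46-fold (AIC) or 1.88-fold (BIC). With only about 100 people, as in one arm, it is 2.07-fold or 2.64-fold.

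**Step 4, simulation check.** Forward selection in linear models used 20 candidates, 3 of them real, n = 200 and 100 to 200 runs per setting. At a true 0.10 the mean kept estimate was 0.159 (AIC) and 0.194 (BIC), and 96% and 100% of kept estimates lay above the truth. Casting the predictors as treatment interactions, with half the slope difference set to 0.10, gave 0.156 and 0.205. The full model without selection averaged 0.094 to 0.103 for a true 0.10 and 0.196 to 0.202 for a true 0.20, so it is close to unbiased.

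**The case against.** The strongest reply is that the protocol never says effect sizes are read from the selected model, or that dropped measures go unreported. This is a condensed article, and an analysis plan not shown here could tabulate every candidate with a CI. That stands as a limit: the link is an inference from the absence of any other described predictor analysis. It does not remove the mismatch, because the method the article commits to does not by itself deliver the estimates the article asks for.

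Three stronger readings are tempting and unsupported.
- A reader might infer that the protocol expects all individual predictors to be weak. The Introduction's remark concerns genetic predictors, and the Design section already concedes limited power for those. Nothing is said about the strength of demographic, clinical or questionnaire predictors.
- A reader might infer that every retained coefficient is materially inflated. The bias is small by 0.20 and negligible by 0.30.
- A reader might infer that the larger study will be undersized. The protocol calls the estimates useful for power calculations; it does not say that they alone set the sample size. The Introduction places the future study in a twin design, and the Sample size section makes variances its main interest. Undersizing follows only if selected coefficients are used uncorrected.

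It is also fair to say that this is a secondary aim of a pilot that admits low power. That admission does not answer the point, since low power makes selection bias larger. Whether ordinary AIC and BIC apply to GEE is a separate question; the bias arises under a full likelihood too.

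**Conclusion.** The concern holds in a conditional form. The stated purpose is to estimate predictor effects for planning, and the one described method is selection of a single model in the same data. If the planning figures come from that model, weak predictors are overstated, by about 1.6-fold (AIC) or 2.0-fold (BIC) at a true effect of 0.10 and n = 200, falling to about 1.06-fold or 1.18-fold at 0.20. The planning consequences in the table rest on the assumed effect sizes, alpha and target power, and on a Gaussian approximation with independent estimates. How large the problem is for the questionnaire measures cannot be known from the document. It is worth correcting before analysis, since supplying planning figures is the declared reason for this aim, but it does not touch the primary objectives.

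**What to change.** State that an effect size with a 95% CI will be reported for every prespecified baseline predictor, from models without variable selection and with a fixed covariate set. Where the predictor is studied as a moderator, the reported quantity should be the predictor-by-arm term. Keep the AIC/BIC-selected model as a descriptive summary. Add a sentence that power calculations for the larger study will use the unselected estimates, or shrunken ones, together with their CIs.

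The cost is a few lines of wording and one extra table, with no new data and no design change. The downside is that the reported effects will look smaller and less certain.
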